##### Client Socioeconomic and Services Receipt Inventory

The assessment of psychosocial and health care service use (as a basis for the estimation of treatment costs for the parents) will be performed by the German version of the “Client Socioeconomic and Services Receipt Inventory” (CSSRI-DE) (61). The CSSRI-DE is an interview including five dimensions (sociodemographic data, living conditions, occupation and income, utilization of health services, and medication). The CSSRI-DE was developed for cost analysis of the psychiatric supply system and allows a comprehensive assessment of all substantial components for direct and indirect costs.

##### Children and Adolescent Mental Health Service Inventory

The German version of the “Children and Adolescent Mental Health Services Receipt Inventory” (CAMHSRI) (62) will be used to assess the health and psychosocial service use as a basis for the assessment of treatment costs for the children.

All interviews and questionnaires are administered at baseline as well as at 6, 12, and 18 months after baseline assessment. Although participants are aware of the group they have been assigned to, the external raters assessing the primary outcome and the health-economics, are not.

The measures to be administered at each time point are listed in Table 2.

**Table 2 T2:** Outcomes and measures.

**Outcome**		**Instrument**		**Source**					**Time (months)**			
		**Questionnaire**	**Interview**	**Patient**	**Partner**	**Child (>10 year)**	**Therapist**	**External rater**	**pre**	**6**	**12**	**18**
Demographics		*Ad hoc* items		x	x				x			
Diagnoses/Psychiatric symptomatology	Parents	Medical history						x	x			
		PHQ-D		x	x				x			
		BSI		x	x				x	x	x	x
		CGI						x	x	x	x	x
		GAF						x	x	x	x	x
	Children	CBCL	Kiddie-SADS-PL	x	x				x	x	x	x
		YSR				x			x	x	x	x
		SGKJ						x	x	x	x	x
Health-related quality of life	Parents	EQ-5D		x	x				x	x	x	x
	Children	Kidscreen-27/-10		x	x	x			x	x	x	x
Family relations and family functioning		FB-A		x	x	x			x	x	x	x
		GARF						x	x	x	x	x
		*Ad hoc* items		x	x	x			x	x	x	x
Coping with the disorder	Parents	FKV		x	x				x	x	x	x
Social support		OSSQ		x	x	x			x	x	x	x
Evaluation of treatment		FBB^*^		x	x	x	x			x	x	x
Health economic assessment of treatment costs	Parents		CSSRI-DE	x	x			x	x	x	x	x
	Children		CAMHSRI-DE	x	x			x	x	x	x	x
Formulation of goals		*Ad hoc* items^*^		x	x	x			x			
Achievement of goals, satisfaction		*Ad hoc* items^*^		x	x	x	x			x	x	x
Therapeutic process		VPPS^*^					x		x^**^			
		*Ad hoc* items^*^					x		x^**^			

* *For intervention group only*.

** *During the intervention*.

#### Randomization Procedure

Computerized lists for familywise randomization with an allocation ratio of 1:1 stratified by centers with a variable block length will be prepared by the Department of Medical Biometry and Epidemiology of the University Medical Center Hamburg-Eppendorf. The subsequent central allocation procedure is managed by the coordinating study center in Hamburg to guarantee allocation concealment.

Randomization will take place once the standardized baseline diagnostics are complete. Thus, every randomized family, both in the intervention and in the control group, will receive comprehensive standardized diagnostics of every participating child.

#### Data Assessment and Data Management

At the beginning of the study (T1; see Figure 1), the mentally ill parent and—if there is one—the partner fill in the baseline questionnaires and participate in the K-SADS-PL interviews about their child/children. All children aged 10 years and older are also asked to complete this diagnostic process. As soon as all documents are completed, the family is randomized to either control or intervention group. The research staff subsequently informs the family about their group assignment and provides feedback on the results of the child's K-SADS-PL interview.

**Figure 1 F1:**
[figure not shown]
Overview of the CHIMPs study design.

If the family has been referred to the intervention group, the therapist who carries out the CHIMPs program is informed and the start of the intervention is initiated. If the family has been referred to the control group, no further treatment is provided within the CHIMPs study.

At 6 (T2), 12 (T3), and 18 (T4) months after baseline assessment, the families will be contacted again by the research staff. The questionnaires and diagnostic interviews for all three follow-up assessments are the same as at the baseline assessment. Families receive a financial compensation (up to €50) if a follow-up assessment is completed, in order to further promote a complete follow-up.

All study-related information will be stored securely at the study site. All records that contain names or other personal identifiers, such as locator forms and informed consent forms, will be stored separately from study records identified by code number. The coordinating study site will oversee the intra-study data sharing process.

All study outcomes, especially the primary outcome papers, will be published in peer-reviewed journals and presented at scientific conferences. All papers and abstracts must be approved by the coordinating site before submission.

### Data Analysis

All data will be entered twice at the coordinating site. Original study forms will be sent to the coordinating site and a copy of them will be kept at the participating site. Participant files will be stored in a secure and accessible place for a period of 3 years after completion of the study.

Data will be analyzed and reported according to the CONSORT statement. Mean and standard deviation will be presented for the continuous variables and absolute and relative frequencies for the categorical variables for the whole sample and separated by treatment groups. Since the relatives of a family are subject to common influences, cluster effects are generally to be expected. Therefore, the inferential statistics will be conducted using mixed models with the family and the relatives as random effects. As further covariates, recruitment center, treatment group, time, and the interaction between the two, as well as baseline variables that are unbalanced between the treatment groups. As further possible covariate, the type of clinic (university clinic vs. supply clinic) will be examined. For this purpose, baseline comparisons will be performed. If significant differences are found, this variable will be included in the model as a further fixed effect. We will use the direct Maximum-Likelihood as the statistical estimation procedure in the intention-to-treat population (ITT), which results in unbiased estimations under the missing-at-random assumption. The ITT analysis will be based on the available clinical data from all randomized families. The primary outcome analysis is the treatment group contrast (CHIMPs vs. TAU) at 18 months after baseline assessment in the ITT population of the children with an initial psychiatric diagnosis according to K-SADS-PL in a mixed logistic regression with the above-mentioned specification. The primary outcome is a psychiatric diagnosis according to K-SADS-PL (yes/no). Only the result of this comparison will be interpreted in a confirmatory manner. Additionally, this analysis will be repeated in the per protocol population. Sensitivity analyses will be performed for the primary outcome analysis with different methods of missing value imputation such as multiple imputation and last observation carried forward (LOCF) to study the robustness of the findings. Odds ratios, their 95% confidence intervals and *p*-values will be reported. The type I error will be set at 5% (two-sided). The secondary outcomes will be examined with appropriate methods in the ITT population in an exploratory manner. As far as possible, these outcomes will be operationalised as difference to baseline. Interim analyses are not planned. Subgroup analysis will be conducted on study sites, children's and adolescents' age and children's and adolescents' gender. A detailed statistical analysis plan will be finalized based on an analysis of a blinded, pooled data set. Statistical analyses will be carried out with SPSS, version 24 or newer (IBM Corp, Armonk, NY, USA) R, version 3.6.3 or newer (R Foundation for Statistical Computing, Vienna, Austria) or SAS, version 9.4 or newer (SAS Institute, Cary, NC, USA).

Cost differences between both study groups will be analyzed by linear regression models (63–65). The adjustment of standard errors in case of deviations from the normal distribution will be performed by non-parametric bootstrapping (65, 66). The cost-effectiveness of the CHIMPs intervention compared to treatment as usual (TAU) will be computed by the net-monetary-benefit method (67–69). Quality adjusted life years (QALYs) will be computed by transforming KIDSCREEN-10 values into Child Health Utility (CHU9D) values (70) using the algorithm provided by Chen and colleagues (71). Incremental cost-effectiveness ratios (ICER) will be calculated to estimate the maximum willingness to pay necessary for the gain of one quality-adjusted life year (QALY) by implementing the CHIMPs intervention in comparison to standard care (69). ICER will be interpreted on the basis of the cost-effectiveness plane (67–69). Stochastic uncertainty of the ICER will be estimated by non-parametric bootstrapping and the cost-effectiveness acceptability curve (67–69).

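### The confirmatory model takes covariates by observed baseline imbalance between arms instead of naming prognostic ones in advance; type I error is safe, but a gain of about 0 to 8 points of power is forgone

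*Protocol article*

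**What the plan says.** All of this stands in the Data Analysis section of the protocol article unless noted.

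- Inference uses "mixed models with the family and the relatives as random effects".
- The fixed part is "As further covariates, recruitment center, treatment group, time, and the interaction between the two", followed by "as well as baseline variables that are unbalanced between the treatment groups". Neither a list of candidate variables nor a definition of imbalance is given.
- Clinic type is handled separately: "the type of clinic (university clinic vs. supply clinic) will be examined" through baseline comparisons, and then "If significant differences are found, this variable will be included in the model as a further fixed effect".
- The primary analysis compares the arms at 18 months among children with an initial K-SADS-PL diagnosis, "in a mixed logistic regression with the above-mentioned specification". It is the only confirmatory comparison, so the covariate rule is part of the confirmatory model.
- On timing: "A detailed statistical analysis plan will be finalized based on an analysis of a blinded, pooled data set".
- Under Randomization Procedure, families are allocated 1:1, "stratified by centers with a variable block length", after baseline diagnostics are complete.

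**The concern.** Three things are unsatisfactory about letting imbalance choose the covariates.

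1. **Wrong criterion.** With concealed central randomisation, a baseline difference between arms is chance. Adjustment helps when a variable predicts the outcome. Imbalance says nothing about that, so the rule can admit noise and will usually leave out a strong predictor.
2. **Wrong moment.** Imbalance between arms cannot be seen in pooled data. An analysis plan finalised on such data could fix candidates and a threshold, but not which variables enter. Under the stated rule the final covariate set is known only once allocation is known.
3. **Shifting target.** An odds ratio conditional on covariates changes meaning with the covariates conditioned on, so the reported effect measure would depend partly on chance.

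At stake are efficiency and clean pre-specification of the one confirmatory test, not its basic validity.

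**Working it through.** **Reproducing the plan's sample size** (Sample Size and Power Calculation: 76% vs 90%, 80% power, two-sided 5%, ICC 0.05, mean of 2 children per family).

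- Design effect: 1 + (2 − 1) × 0.05 = 1.05.
- Unpooled two-proportion formula: (1.960 + 0.842)² × (0.76 × 0.24 + 0.90 × 0.10) / 0.14² = 109.08 per group.
- 109.08 × 1.05 = 114.5 children, or 57.3 families, so 58 families and 116 children per group. This matches the article. The calculation contains no covariate adjustment.

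**How often chance flags something.** If k independent variables were each tested at 5%, P(at least one flagged) = 1 − 0.95^k: 23% for k = 5, 40% for 10, 64% for 20, 79% for 30. Both k and the 5% are assumptions.

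**Power and type I error.** Simulation settings:

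- 120 families of 2 children; marginal rates 90% vs 76% (90% in both arms under the null).
- 10 candidate covariates, of which one is prognostic.
- Logistic regression with family-robust standard errors; 3,000 runs per setting.
- Imbalance rule taken as p<0.05.
- Log odds ratio of the prognostic variable varied from 0 to 1.5 per SD, because the documents give no value.

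| Log-OR per SD | Power, no adjustment | Power, imbalance rule | Power, one pre-specified covariate | Gain forgone (points) | Type I error, imbalance rule |
|---|---|---|---|---|---|
| 0 | 82.6% | 82.4% | 82.6% | 0.2 | 4.7% |
| 0.5 | 82.2% | 81.6% | 83.3% | 1.7 | 3.8% |
| 1.0 | 83.1% | 83.0% | 86.6% | 3.6 | 4.5% |
| 1.5 | 81.7% | 81.8% | 89.5% | 7.7 | 4.2% |

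The prognostic variable was selected in only about 5% of runs. Monte Carlo standard error on power is about √(0.83 × 0.17 / 3000) = 0.7 points. The simulation left out centre terms and repeated visits and did not fit the mixed model itself.

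**Room for covariates.** Expected children without a diagnosis at 18 months: 116 × (0.24 + 0.10) = 39.4. Adjusting for all 10 candidates, 9 of them noise, gave type I error of 5.2% to 5.9%, against 4.5% to 4.8% with one pre-specified covariate. A short list is therefore preferable.

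**Clinic type.** Intercept, treatment and six centre indicators give 8 columns.

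- With one clinic type per centre, adding clinic type gives 9 columns of rank 8, so the term is fully aliased with centre.
- If one centre recruits at both types, the rank is 9 and the term is estimable.
- With centre-stratified blocks (sizes 4 and 6, 115 families in each of 7 centres), a significant arm difference in clinic type occurred in 0 of 4,000 simulations. This concerns all randomised families; the diagnosed subset is not balanced as tightly.

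**The case against.** The best defence is that most of the model is fixed: population, endpoint, time point, contrast, random effects, estimation method, centre, treatment, time and interaction. Only supplementary covariates are open. They are measured before randomisation and would be chosen without looking at outcomes. A candidate list and a definition of imbalance are details that an analysis plan usually supplies, and that plan is not shown. This stands as far as it goes, but it does not rescue the rule. The article does not merely leave a detail open; it states a selection principle, and that principle cannot be carried out on pooled data.

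Several stronger readings are tempting and are not supported:

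- **That all covariates are chosen by significance testing.** The significance condition is written only for clinic type. For the other variables the text says only that they are unbalanced.
- **That type I error is inflated.** A mechanical rule showed no inflation. The effect of a discretionary choice cannot be quantified from the documents.
- **That the planned 80% power is eroded.** That power was computed without covariates, and the rule performs about like no adjustment. What is lost is a possible gain.
- **That the clinic-type term is certainly redundant.** This needs fixed centre effects and one clinic type per centre. The wording about a further fixed effect and the Study Centers list suggest both, but neither is stated outright, and Recruitment does not tie hospital type to centre.
- **That the clinic-type comparison is between arms.** The Discussion's concern about recruitment differences suggests it may be between clinic types, which could be examined on blinded data.

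**Conclusion.** The point holds for the clause on unbalanced baseline variables. It ties covariates of the only confirmatory test to chance arm differences, and membership of the set cannot be fixed on the data named for finalising the analysis plan. The cost is a forgone gain of about 0 to 8 points of power, depending on an assumed prognostic strength of 0 to 1.5 log odds per SD and on reading the rule as p<0.05. Validity under a mechanical rule is not threatened, so this is an inexpensive improvement and not a fatal flaw.

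The clinic-type gate is secondary. If centre is fixed and each centre has one clinic type, the term is aliased and leaves the treatment contrast unchanged. Otherwise it is estimable, but a significance test is still a poor way to decide its entry.

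**What to change.** - Delete the imbalance rule. Use baseline tables descriptively.
- Before unblinding, name a very short list of prognostic baseline variables, included regardless of balance alongside centre, treatment, time and treatment × time. Examples are child age, gender and one baseline severity score such as the SGKJ. The CBCL is a less convenient choice because the article describes it for ages 4 to 18 while children aged 3 to 19 are eligible.
- Keep the list short, given about 39 expected children without a diagnosis.
- Remove the significance gate for clinic type. State whether centre is a fixed effect and whether any centre recruits at both types. If none does, keep centre alone; if one does, decide in advance whether clinic type enters.

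The cost is wording in the protocol and analysis plan. The variables are collected before randomisation, and the sample size does not change.

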#### Sample Size and Power Calculation

The primary analysis is based on the intention-to-treat population of all children and adolescents with initial psychiatric diagnosis (addressed in hypothesis 4). In a first step, we calculated the number of children and adolescents to demonstrate the assumed effect in this population. Since the intervention takes place at family level, we determined the total number of children and adolescents and their families to be recruited in a second step.

We assume that 18 months after the baseline assessment 76% of children and adolescents in the intervention group and 90% in the control group still have a psychiatric diagnosis according to K-SADS-PL. Further, we suppose that 25/55/15/5% of the families have 1/2/3/4 children, so that on average a family has 2 children and adolescents. With a power of 80%, a two-sided alpha of 5% and an intracluster correlation of 0.05, we need 116 children and adolescents per group (232 children and adolescents in total) with an initial psychiatric diagnosis in 58 families per group (116 families in total) to detect this difference. We rounded up to 240 children and adolescents in 120 families. Additionally, we expect that 15% of children and adolescents show an initial psychiatric diagnosis according to K-SADS-PL. With this assumption, we have to recruit in total 800 families with 1,600 children and adolescents.

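### The two named robustness checks are a weak test of missing-at-random, and LOCF in a set where every child is ill at baseline can turn unequal early drop-out into an apparent effect

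*Protocol article*

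**What the plan says.** Three statements in the protocol article bear on this point.

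- **Assumption.** Under Data Analysis, the 18-month comparison of CHIMPs with treatment as usual (TAU) is estimated by direct maximum likelihood in a mixed logistic regression, said to give "unbiased estimations under the missing-at-random assumption". It is the only confirmatory comparison.
- **Population.** Under Sample Size and Power Calculation, the primary analysis uses the "intention-to-treat population of all children and adolescents with initial psychiatric diagnosis". Data Analysis repeats this restriction. The outcome is presence or absence of a K-SADS-PL diagnosis, so its baseline value is yes for every child analysed.
- **Robustness.** Under Data Analysis, sensitivity analyses of the primary outcome will use "different methods of missing value imputation such as multiple imputation and last observation carried forward (LOCF) to study the robustness of the findings".

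Follow-up visits are at 6, 12 and 18 months. No drop-out rate is given. A detailed analysis plan is announced in the same section but is not at hand.

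**The concern.** A sensitivity analysis for missing data should show how far the conclusion depends on an assumption that the data cannot verify. Here that assumption is that, given what has been observed, children who drop out have the same 18-month outcome distribution as those who stay.

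Standard multiple imputation shares the assumption, so its agreement with the likelihood analysis says little about informative drop-out. LOCF does depart from it, but by one arbitrary rule. In this population the rule amounts to coding a missing outcome as ill for every child lost before month 6. A child last seen at month 6 or 12 carries that later status, which may be no diagnosis.

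Under LOCF a lower drop-out rate in one arm therefore looks like more recovery in that arm. The check could appear to confirm an effect, or cast doubt on one, because of retention alone. Participants know their allocation and control families receive no further treatment within the study, so unequal retention is possible, though the article does not show that it will occur.

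**Working it through.** **Inputs from the article** (Sample Size and Power Calculation): "76% of children and adolescents in the intervention group and 90% in the control group still have a psychiatric diagnosis" at 18 months; "With a power of 80%, a two-sided alpha of 5% and an intracluster correlation of 0.05"; mean family size 2; 120 children per group after rounding up.

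**Assumed inputs:** the share of children lost before month 6, taken as 10% to 30%; the true persistence in the no-effect examples; and, for simplicity, no loss after month 6.

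**1. The plan's own figure.** Unpooled two-proportion formula:

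n = (1.960 + 0.842)² × (0.76×0.24 + 0.90×0.10) / 0.14² = 109.1 per group.

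Design effect 1 + (2 − 1)×0.05 = 1.05, and 109.1 × 1.05 = 114.5, which is 116 in whole families of two. The stated 116 per group is reproduced, so no design figure is in dispute. The planned odds ratio is (0.76/0.24)/(0.90/0.10) = 0.352.

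**2. What LOCF does.** Let d be the share lost early and p the persistence among the rest. Then

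LOCF proportion ill = d + (1 − d)p, and LOCF proportion recovered = (1 − d)(1 − p).

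The ratio of recovery between arms is thus multiplied by the ratio of retention, (1 − d₁)/(1 − d₀). With equal loss that factor is 1. With unequal loss it is not.

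**3. Equal early loss, planned rates 76% and 90%**

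| Loss in each arm | CHIMPs | TAU | Difference (points) | Odds ratio |
|---|---|---|---|---|
| 0% | 76.0% | 90.0% | 14.0 | 0.352 |
| 10% | 78.4% | 91.0% | 12.6 | 0.359 |
| 20% | 80.8% | 92.0% | 11.2 | 0.366 |
| 30% | 83.2% | 93.0% | 9.8 | 0.373 |

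The risk difference shrinks. The odds ratio, which is the measure the plan reports, barely changes.

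**4. Unequal early loss**

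| True persistence (CHIMPs / TAU) | Loss (CHIMPs / TAU) | LOCF result | Odds ratio | True odds ratio |
|---|---|---|---|---|
| 80% / 80% | 10% / 30% | 82% / 86% | 0.74 | 1 |
| 80% / 80% | 15% / 25% | 83% / 85% | 0.86 | 1 |
| 90% / 90% | 10% / 30% | 91% / 93% | 0.76 | 1 |
| 90% / 90% | 30% / 10% | 93% / 91% | 1.31 | 1 |
| 76% / 90% | 30% / 10% | 83.2% / 91% | 0.490 | 0.352 |
| 76% / 90% | 10% / 30% | 78.4% / 93% | 0.273 | 0.352 |

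First row: 0.9×0.80 + 0.1 = 0.82 and 0.7×0.80 + 0.3 = 0.86, so the odds ratio is (0.82/0.18)/(0.86/0.14) = 0.74.

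**5. A departure that neither check explores.** Suppose 76% and 90% are seen among children still observed, all CHIMPs drop-outs are ill, and TAU drop-outs resemble the observed TAU children. With 120 per group and design effect 1.05, early loss of 10%, 20% and 30% in each arm gives odds ratios of 0.403, 0.468 and 0.550, with p = 0.016, 0.049 and 0.131. At the same loss rates LOCF gives p = 0.008, 0.014 and 0.022. LOCF would look reassuring where an arm-specific departure removes significance.

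All odds ratios here are marginal, computed from proportions. The mixed model's family-conditional odds ratio would differ somewhat.

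**The case against.** The other side has several good points.

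- **The list is open and an analysis plan is announced.** The wording gives examples, and delta-adjusted analyses commonly appear in the analysis plan. A reader might infer that the trial has no analysis under missing-not-at-random. The article does not support that. What can be criticised is the stated choice of LOCF for this population.
- **LOCF is not a missing-at-random method.** A reader might infer that the named checks never leave that assumption. They do, once, by the same rule in both arms and with no variation in size or direction. The check is limited, not absent.
- **LOCF does not erase the treatment effect.** With equal loss the odds ratio is nearly unchanged. To say that the LOCF result reflects drop-out instead of the intervention goes too far; it mixes the two.
- **Control families are not abandoned.** Data Assessment and Data Management withholds only further treatment. Follow-up contact and payment of up to €50 per completed assessment are not limited to one arm, and the Discussion promises referral in both groups where indicated. Differential loss is possible but not documented.
- **The examples are simplified.** Placing all loss before month 6 maximises the distortion, and 80% persistence is not a planning figure. Even 82% against 86%, with 120 per group and design effect 1.05, gives z of about 0.83 and p of about 0.41. That contrast alone would not reach significance.

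All of these stand. They narrow the point but do not remove it: LOCF is named, the baseline value is fixed at ill by the definition of the population, and the resulting bias can go in either direction.

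**Conclusion.** The point holds in a limited form. The two named checks are a weak test of the missing-at-random assumption. One repeats it. The other replaces it with a single fixed rule that, for children with no follow-up value, can produce an apparent effect from unequal retention: odds ratios of about 0.74 to 1.31 where the truth is 1, for assumed early losses of 10% and 30%. With equal loss the effect on the odds ratio is negligible.

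These sizes rest on assumed loss rates and on all loss falling before month 6. Later loss would dilute them, because those children carry a 6- or 12-month status.

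A reader might conclude that LOCF could create or hide the trial's main finding. It cannot: only the maximum-likelihood comparison is confirmatory, and it is unaffected. What suffers is the evidence offered for its robustness. The change is worth making before the analysis plan is final, but the point does not threaten the primary analysis.

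**What to change.** Remove LOCF as a named sensitivity analysis for the primary outcome and specify instead:

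1. Multiple imputation with auxiliary variables that Table 2 already schedules at every visit: CBCL, YSR (children aged 10 and older only), SGKJ and earlier K-SADS-PL results.
2. A delta-adjusted version that shifts the log-odds of a diagnosis for missing 18-month outcomes, separately by arm, over a range stated in advance.
3. The tipping point, meaning the combination of shifts at which the primary conclusion changes, reported with a judgement on whether such shifts are plausible.

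Children lost before month 6 have only baseline auxiliaries, so for them the delta adjustment carries most of the weight. Retention by arm and visit should be shown alongside.

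The cost is a few lines in the analysis plan, modest extra programming and the need to justify a delta range. No new data are needed, and neither the sample size nor the primary model changes.

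### Continuous secondary outcomes are planned as change from baseline without a prespecified baseline covariate, which costs precision mainly in hypotheses 3 and 5

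*Protocol article*

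**What the plan says.** All statements on the model are in the protocol article, Data Analysis.

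- Form of the outcome: "As far as possible, these outcomes will be operationalised as difference to baseline".
- Status and method: "The secondary outcomes will be examined with appropriate methods in the ITT population in an exploratory manner".
- Model: "the inferential statistics will be conducted using mixed models with the family and the relatives as random effects".
- Covariates: "As further covariates, recruitment center, treatment group, time, and the interaction between the two", followed by "as well as baseline variables that are unbalanced between the treatment groups".
- What is still to come: "A detailed statistical analysis plan will be finalized based on an analysis of a blinded, pooled data set".

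Baseline scores will be available. The section on the child service inventory states that "All interviews and questionnaires are administered at baseline as well as at 6, 12, and 18 months after baseline assessment", and Randomization Procedure states that "Randomization will take place once the standardized baseline diagnostics are complete".

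The hypotheses with a continuous outcome are 1 (CBCL and KIDSCREEN, all children), 3 (KIDSCREEN, children above the CBCL cut-off at baseline) and 5 (KIDSCREEN, children with a K-SADS-PL diagnosis at baseline).

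**The concern.** The text fixes two things together: the response is a difference to baseline, and a baseline variable becomes a covariate only when the arms differ on it. Subtracting the baseline forces its coefficient to be 1. Regression adjustment lets the data estimate that coefficient and is at least as precise in a randomised comparison. The trial therefore collects a strong predictor for every child and uses it inefficiently.

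The imbalance rule does not repair this. The gain in precision from adjustment comes from the correlation between baseline and follow-up, whether or not the arms happen to differ. The rule may also admit the baseline score for some outcomes and not for others. Imbalance between arms cannot be seen in the blinded, pooled data on which the SAP is to be finalised, so the rule can be applied only once the group data are in use.

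At stake is the width of the confidence intervals for the quality-of-life and symptom scales, above all in the two baseline-defined subsets, where the numbers are smallest.

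**Working it through.** **Inputs from the protocol article (Sample Size and Power Calculation; Data Analysis).** Two-sided alpha 5%; intracluster correlation 0.05; families with 1/2/3/4 children in 25/55/15/5%, mean 2; 1,600 children in all, 400 with initial mental health problems and 240 with an initial diagnosis; 1:1 allocation; 0.25 SD for continuous outcomes in the whole sample.

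**Assumptions, not in the document.** The baseline to follow-up correlation r; equal SDs at the two times (relaxed below); 0.25 SD of the raw score as the effect in the two subsets as well; one follow-up time; the same intracluster correlation for raw and adjusted scores.

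**Step 1: the plan's own figures.** The design effect is 1 + (2 − 1) × 0.05 = 1.05, or 1.065 allowing for varying family size.

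- Primary: (1.96 + 0.842)² × (0.76 × 0.24 + 0.90 × 0.10) / 0.14² = 109.1 per arm; × 1.065 = 116.2. The plan states 116.
- Hypothesis 2: 80% against 90% with 200 per arm gives 78.8%. The plan states 79%.
- Hypothesis 1: 0.25 SD with 800 per arm and design effect 1.05 gives 99.8%. The plan states at least 80%.

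The figures reproduce, so a design effect of 1.05 is a fair basis for the rest.

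**Step 2: variance per child, in units of the follow-up variance.**

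- Unadjusted change score: 1 + 1 − 2r = 2(1 − r).
- Baseline as covariate: 1 − r².
- Ratio: 2(1 − r) / [(1 − r)(1 + r)] = 2/(1 + r), which exceeds 1 for every r below 1.

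For r below 0.5, 2(1 − r) exceeds 1, so the change score is noisier than the follow-up score used alone.

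**Step 3: power for 0.25 SD.** SE = √(variance × 2 × 1.05 / n per arm). Example at r = 0.6 and 120 per arm:

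- Change: √(0.80 × 2.1 / 120) = 0.1183; 0.25/0.1183 − 1.96 = 0.153; power 56.1%.
- Adjusted: √(0.64 × 2.1 / 120) = 0.1058; 0.25/0.1058 − 1.96 = 0.402; power 65.6%.

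| r | Variance ratio | 400 children: change / adjusted | 240 children: change / adjusted |
|---|---|---|---|
| 0.3 | 1.54 | 54.1% / 72.5% | 35.8% / 50.8% |
| 0.5 | 1.33 | 68.4% / 80.4% | 47.2% / 58.8% |
| 0.6 | 1.25 | 77.9% / 86.2% | 56.1% / 65.6% |
| 0.7 | 1.18 | 88.3% / 92.7% | 68.4% / 75.4% |

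In the whole sample (800 per arm) the change score still has 98.5% power at r = 0.3, and 93.2% even at r = 0.

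**Step 4: unequal SDs.** With k = baseline SD / follow-up SD, the ratio is (1 + k² − 2rk)/(1 − r²) = 1 + (k − r)²/(1 − r²). It is never below 1 and equals 1 only when k = r. At r = 0.6:

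- k = 1: 1.25
- k = 0.9: 1 + 0.09/0.64 = 1.14
- k = 0.8: 1 + 0.04/0.64 = 1.06
- k = 1.1: 1 + 0.25/0.64 = 1.39

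The direction of the loss is therefore general, but its size depends on both r and k.

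**The case against.** The strongest reply is that defining the outcome as a change does not exclude a baseline covariate. With the covariate in the model, the treatment estimate is the same for change and for follow-up value. On this view the complaint rests on silence about one model term for exploratory outcomes, which is ordinary SAP content, and the text leaves room through its wording on feasibility and on suitable methods. Part of this stands: the SAP is not shown and may add the term. But the article is not merely silent. It lists the covariates for its mixed models and gives the condition under which baseline variables join them. An SAP that follows that condition would leave the baseline score out unless imbalance is found.

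A reader might also infer more than the document supports:

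- *That no baseline score can be in the model.* The imbalance rule could admit it.
- *That the change score is biased, through regression to the mean, in children chosen for being ill.* Selection uses baseline assessments completed before randomisation and applies to both arms alike, so average regression to the mean cancels in the contrast. Hypotheses 3 and 5 are also selected on CBCL or K-SADS-PL, while their outcome is KIDSCREEN. What remains is chance difference between arms, which affects precision and is partly covered by the imbalance rule.
- *That hypothesis 1 is underpowered.* With 1,600 children it is not.
- *That the trial's conclusion is at risk.* Only the primary K-SADS-PL comparison is confirmatory, and it is a binary outcome in a logistic model.

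The article makes no power claim for hypotheses 3 or 5 and gives 0.25 SD only for the whole sample, so the subset figures illustrate the loss and correct no stated number.

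**Conclusion.** The point holds as one of efficiency and prespecification. The planned analysis is valid, but for continuous secondary outcomes it is less precise than one the trial can run on the same data, and whether the baseline score is used is left to a data-driven rule.

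With equal SDs, the variance is 18% to 54% larger for r from 0.7 to 0.3; a baseline SD modestly below the follow-up SD makes this smaller. The matching loss of power is about 4 to 18 percentage points with 400 children and 7 to 15 with 240. These figures rest on assumed values of r, the SD ratio and the subset effect, and they apply where the imbalance rule does not bring the baseline score in. For hypothesis 1 the practical consequence is a wider interval. Because the affected analyses are exploratory, this is a worthwhile improvement and not a threat to the trial.

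**What to change.** State in the SAP that each continuous secondary outcome is modelled with its own baseline value as a fixed covariate, whether the response is the value at 6, 12 and 18 months or the change. Keep the family and child random effects, centre, and treatment by time. State also that including this covariate does not depend on observed imbalance. Results can still be reported as differences to baseline.

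The cost is about one sentence. It needs no new data, visits or participants, because the baseline questionnaires are already part of the schedule and baseline diagnostics precede randomisation. The SAP was still to be finalised when the article was written, so it is the natural place for the change.
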